## Abstract

**Background:**

Comprising of both organisational and patient level components, collaborative care is a potentially powerful intervention for improving depression treatment in UK primary Care. However, as previous models have been developed and evaluated in the United States, it is necessary to establish the effect of collaborative care in the UK in order to determine whether this innovative treatment model can replicate benefits for patients outside the US. This Phase III trial was preceded by a Phase II patient level RCT, following the MRC Complex Intervention Framework.

**Methods/Design:**

A multi-centre controlled trial with cluster-randomised allocation of GP practices. GP practices will be randomised to usual care control or to "collaborative care" - a combination of case manager coordinated support and brief psychological treatment, enhanced specialist and GP communication. The primary outcome will be symptoms of depression as assessed by the PHQ-9.

**Discussion:**

If collaborative care is demonstrated to be effective we will have evidence to enable the NHS to substantially improve the organisation of depressed patients in primary care, and to assist primary care providers to deliver a model of enhanced depression care which is both effective and acceptable to patients.

**Trial Registration Number:**

ISRCTN32829227

## Background

Depression is a major health problem causing substantial disability and set to become the second largest cause of global disability by 2020 [1,2]. Despite the availability of effective pharmacological and psychological treatments for depression, patients often receive a less than optimal treatment programme. In primary healthcare systems internationally, patient adherence with pharmacological treatment is poor [3] and problems are exacerbated further by organisational barriers between generalist and specialist mental health professionals [4,5]. Generalist primary care physicians often have very limited support when helping patients with both pharmacological treatment and psychosocial interventions. Such support may be critical given that in systems such as that in the United Kingdom (UK) and elsewhere, the general practitioner (GP) is the sole responsible medical clinician for 90-95% of patients [6].

Attempts to improve this situation have seen the development of organisational strategies including increased resources to specialist services, education of primary care clinicians, consultation liaison services and stepped care [7]. A systematic review of 36 organisational intervention studies concluded that simple models such as guidelines and education were ineffective in improving the management of depression [8]. Gunn et al [9] identified the components of effective organisational quality improvement strategies as: a multi-professional approach to patient care; a structured management plan; scheduled patient follow-ups; and enhanced inter-professional communication.

One model which has seen an increasing efficacy and effectiveness literature is 'collaborative care' [7] which highlights the chronic nature of depression and proposes that the whole system of care for depression needs to be reengineered. Collaborative care is a complex combination of clinician and patient education, consultation-liaison between primary and secondary care clinicians and case management [10], translated into practice by the introduction of a new case manager role into primary care who liaises between primary care clinicians and mental health specialists, collects and shares information on the clinical care of individual patients and delivers and manages aspects of their care [7].

Whilst collaborative care improves outcomes over usual care [11-13], the vast majority of models have been developed and evaluated in the United States (US) [14]. Given this, it is necessary to establish the international generalisability of collaborative care to determine if these outcomes can be replicated beyond the US, where the nature of patient populations and patterns of service utilization may differ. The feasibility and acceptability of implementation in the UK National Health Service (NHS) is likely to be shaped by funding arrangements, deployment of staff and the structure and organization of component parts of the NHS (particularly primary care).

In order to investigate collaborative care in the UK, we adopted the UK Medical Research Council's (MRC) [15,16] strategy for the investigation of complex interventions. Through a series of exploratory qualitative and quantitative studies as part of a 'Trial Platform' funded by the Medical Research Council [17-20] we found collaborative care to have a moderate to large effect (0.63; 95% confidence interval = 0.18 to 1.07), the first time this has been demonstrated in the UK, with change in PHQ-9 scores achieved by the intervention patients from baseline to follow up equating to a clinical shift of almost two categories of depression severity. We also found that the best method of recruitment was through case finding and that collaborative care was acceptable to patients and mental health workers. As a consequence, we have designed a fully powered trial of collaborative care as the next step in our phased approach to investigating this complex intervention.

## Methods/Design

### Objectives

Is collaborative care more clinically and cost effective than usual care in the management of patients with moderate to severe depression in UK primary care?

### Study Design

This is a pragmatic cluster randomised controlled trial with allocation of clusters (GP practices) to two alternative branches (see Figure 1)

**Figure 1 F1:**
[figure not shown]
**Consort diagram detailing progression through the trial**.

1) Collaborative care (experimental group)

2) Usual management of depression (control group)

The rationale for a cluster randomised trial comes from data collected in our trial platform [19] where we tested directly for the presence of contamination between experimental and control conditions. In this pilot phase, after initially randomising General Practices to treatment or cluster control conditions, patients in the treatment cluster group were then individually randomised to either collaborative care or usual care control. This created three study groups (cluster-randomized controls, individually-randomized intervention patients, individually-randomized control patients). Our results showed evidence for substantial contamination, in that when compared to the intervention group's outcomes, patients in the patient-randomised control group (who received no direct patient-level interventions, but may have benefited from organisational effects at the cluster level) had better outcomes (coefficient = -2.99 95% CI -7.56 to 1.58, p = 0.186) than those in the cluster-randomised control who received neither patient- nor organisational-level intervention (coefficient = -4.64; 95% CI -7.93 to -1.35, p = 0.008). The intra-class correlation co-efficient (ICC) for our primary outcome was 0.06 (95% CI = 0.00 to 0.32). This suggests that the effect of the intervention was partly mediated through organisational effects. Therefore, we had to conclude that a patient-randomised trial of collaborative care could be vulnerable to contamination and open to type II error - underestimating the true effect size of the intervention through potential intervention 'leakage'. As a consequence, a cluster-randomised controlled trial design is the safest in order to minimise this potential source of bias and provide a truer estimate of the collaborative care intervention effect size.

### Recruitment of GP practices

We will recruit 48 GP practices in three different recruitment sites: Manchester, London and Bristol, each site responsible for the recruitment of 16 practices. All GP practices in the local Primary Care Trust (PCT) will be eligible for inclusion.

### Randomisation of GP Practices

We will allocate practices by minimisation, with a random element, on centre, deprivation and practice size. We will use the Index of Multiple Deprivation 2007 [21] to assess the level of deprivation in each practice.

## Patient Recruitment

### Sample Size

We have powered this trial to detect an effect size of 0.4. Our effect size is towards the conservative end of our platform trial confidence interval [19] SMD: 0.63; 95% CI 0.18 to 1.07, an effect size achieved by Pilling et al [22] SMD 0.42; 95% CI -0.05 to +0.89, and in line with the findings of recent reviews [23] and our group's recent meta regression [14]. An effect size of 0.4 is also regarded as the most reasonable for determining differences between interventions that are clinically meaningful [24]. Such an effect size at 90% power (alpha 0.05) would require 132 patients per group in a two armed patient randomised trial. For the proposed cluster trial, with 14 patients per cluster and the ICC found in our trial platform of 0.06, the design effect would be 1.65. The cluster trial sample size is, therefore, 440. In order to follow up 440 patients, we will recruit and randomise 550 patients to anticipate a loss to follow up of 20%.

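### The stated design effect of 1.65 does not follow from 14 patients per cluster and an ICC of 0.06 (they give 1.78), and 14 per cluster does not fit 48 practices; the text needs reconciling, but the 48-practice layout is not shown to be underpowered.

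*Protocol article*

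**What the plan says.** The Sample Size section of the protocol article builds the target in steps.

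- Effect size: "We have powered this trial to detect an effect size of 0.4".
- Before clustering: "Such an effect size at 90% power (alpha 0.05) would require 132 patients per group in a two armed patient randomised trial".
- Allowance for clustering: "with 14 patients per cluster and the ICC found in our trial platform of 0.06, the design effect would be 1.65".
- Number to be analysed: "The cluster trial sample size is, therefore, 440".
- Allowance for loss: "In order to follow up 440 patients, we will recruit and randomise 550 patients to anticipate a loss to follow up of 20" per cent.

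Two other places bear on these figures. The text under Figure 1 reports the pilot estimate: "The intra-class correlation co-efficient (ICC) for our primary outcome was 0.06 (95% CI = 0.00 to 0.32". The section on recruitment of GP practices fixes the number of clusters: "We will recruit 48 GP practices in three different recruitment sites", 16 per site.

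The article does not say whether 14 counts patients recruited or patients followed up. It mentions no adjustment for unequal practice sizes.

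**The concern.** The article prints both the inputs to the design effect and the result, and the two disagree. The totals of 440 and 550 are derived from that result, so the 90% power claim cannot be reproduced from the stated inputs. The cluster size of 14 also conflicts with the number of practices given two sections earlier.

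This is not a detail that an article may leave to a fuller document. The figures are stated, they contradict each other, and the sample-size justification depends on them. If the stated cluster size and ICC were both right, the target would be about 6% too small. If the cluster size is wrong, the design effect and power should be restated from the real structure.

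**Working it through.** **Inputs.** Effect size 0.4, 90% power, alpha 0.05, 132 per group, 14 per cluster, ICC 0.06, design effect (DE) 1.65, 440 followed up, 20% loss and 550 recruited (all Sample Size); 48 practices (Recruitment of GP practices). The ICC of 0.06 is confirmed in the text under Figure 1. Alpha is taken as two-sided, because that reproduces 132; one-sided would give 108.

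**1. Steps that reproduce.**
- Per group: 2 × (1.96 + 1.2816)² / 0.4² = 131.3, rounded up to 132; total 264.
- From design effect to sample size: 264 × 1.65 = 435.6, close to the stated 440.
- Loss to follow-up: 440 / 0.8 = 550, exact.

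**2. The step that does not.** DE = 1 + (m − 1) × ICC = 1 + 13 × 0.06 = 1.78.
- Needed: 264 × 1.78 = 469.9, so 470 followed up; 470 / 0.8 = 587.5, so 588 recruited.
- Power at 440: effective size 440 / 1.78 = 247.2; 0.4 × √(247.2 / 4) = 3.144; Φ(3.144 − 1.96) = 88.2%. With 14 followed up, 440 patients come from 440 / 14 = 31.4 practices; a t reference with about 30 df gives about 86%.

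**3. What would give 1.65.**
- At ICC 0.06: m = 1 + 0.65 / 0.06 = 11.83.
- At m = 14: ICC = 0.65 / 13 = 0.05 exactly, which contradicts the 0.06 stated in two places.
- Reading 14 as recruited, with 14 × 0.8 = 11.2 followed up: 1 + 10.2 × 0.06 = 1.612, and 264 × 1.612 = 426. This gives neither 1.65 nor 440.
- Unequal cluster sizes would raise the figure above 1.78, not lower it.

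**4. Fit with 48 practices.**
- 550 / 48 = 11.5 recruited and 440 / 48 = 9.2 followed up per practice.
- 14 × 48 = 672 patients.
- At 14 per practice, 550 patients fill 550 / 14 = 39.3 practices and 440 fill 31.4.

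**5. Power of the layout as planned.** With m = 440 / 48 = 9.17, DE = 1 + 8.17 × 0.06 = 1.49. The number needed is 264 × 1.49 = 393.4, so 394. At 440, the effective size is 440 / 1.49 = 295.3; 0.4 × √(295.3 / 4) = 3.437; power is 93.0% (normal) or 92.0% (t, 46 df).

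**6. Unequal practice sizes.** The documents give no coefficient of variation (CV) of cluster size, so the values below are assumptions. DE = 1 + ((1 + CV²) × 9.17 − 1) × 0.06.

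| Assumed CV | DE | Power, normal | Power, t (46 df) |
|---|---|---|---|
| 0 | 1.49 | 93.0% | 92.0% |
| 0.3 | 1.54 | 92.2% | 91.2% |
| 0.5 | 1.63 | 90.8% | 89.6% |
| 0.65 | 1.72 | 89.2% | 87.9% |

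**The case against.** The strongest reply grants the arithmetic and disputes the consequence.

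- **The planned structure has enough power.** With 48 practices and 440 followed up, power exceeds the claimed 90% if practices are of equal size. This stands.
- **Fourteen is only an input to the design effect.** A reader might infer that sites will recruit 14 per practice, reach 550 in about 39 practices and so lose power. Nothing in the article makes 14 a recruitment target or tells sites to stop there, and 48 practices are fixed. Even in that case, 11.2 followed up per practice gives a design effect of 1.612 and power of about 91% (normal) or 90% (t, 37 df). The 88% and 86% belong to a different case: 14 followed up in about 31 practices.
- **The faulty input is not identified.** It is tempting to conclude that 14 is the slip, since 12 per cluster at ICC 0.06 gives 1.66 and is near 550 / 48. But ICC 0.05 with 14 gives exactly 1.65, so the documents do not support naming one culprit.
- **The planned analysis adjusts for baseline score, and the calculation takes no credit for it.** The article states no baseline–outcome correlation. If it were 0.25, with the ICC held at 0.06, the 470 would fall to 470 × (1 − 0.25²) = 441; at 0.3 to 428; at 0.5 to 352 or 353. This softens the consequence but does not make 1.65 follow from its inputs.

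None of these points removes the inconsistency.

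**Conclusion.** The point holds as an error in the written justification. The stated inputs give a design effect of 1.78, not 1.65. On those inputs the target is 30 short among those followed up (470 against 440) and 38 short among those recruited (588 against 550), and power is about 2 points below the claim by the normal approximation or 4 by the t. Separately, 14 per cluster is incompatible with 48 practices and either total.

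A reader might go further and conclude that the trial is underpowered. The documents do not support that: 48 equal practices with 440 followed up give about 93% (normal) or 92% (t). Power is about 90 to 91% at an assumed CV of 0.5 and passes below 90% only with greater variation in size than that (slightly sooner on the t reference).

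These figures assume two-sided alpha, no gain from baseline adjustment, and an ICC of exactly 0.06, as the article takes it. The pilot interval for that ICC runs from 0.00 to 0.32.

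**What to change.** Reconcile cluster size, ICC and design effect with each other and with the 48 practices. The trial team should confirm from its own calculation which input was misprinted or misapplied, and say whether the cluster size counts patients recruited or followed up.

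Then restate the paragraph from the planned structure: 48 practices, about 9 followed up in each, ICC 0.06, design effect 1.49, and power of about 93% (normal) or 92% (t, 46 df) for 440 patients with equal practice sizes. If an allowance for unequal sizes is added, state the assumed CV and its source.

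Keep 440, 550 and all 48 practices. The cost is a change of wording and a corrected power statement; no patients, practices or analyses are added.

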### Patient inclusion criteria

We will include patients meeting the diagnostic criteria for depression who are aged 18 years and above and who are not currently receiving treatment for depression from specialist mental health services. We will establish the diagnosis of depression by the use of the Clinical Interview Schedule (CIS-R) [25] undertaken by a research worker. We will include both patients newly identified as depressed, with or without one or more previous depressive episodes, and those with an existing diagnosis of depression which is not responding to primary care management. We will also include patients who are suffering from peri- or post-natal depression, with either co-morbid physical illness or co-morbid non-psychotic functional disorders, such as anxiety. In line with the pragmatic nature of this trial, we will reflect usual GP care and participants will be eligible to participate whether they are in receipt of antidepressant medication or not.

### Patient Exclusion Criteria

We will exclude patients whose risk of suicide is sufficiently acute to demand immediate management by a specialist mental health crisis team. We will exclude patients with psychosis, both type I and type II bi-polar disorder, patients where the low mood is better explained by the death of someone close to them and patients whose primary presenting problem is alcohol or drug abuse. Patients who are currently receiving specialist treatment for their depression will also be excluded.

### Patient Identification and Recruitment

Cluster trials are vulnerable to selection bias through systematic differences in referral behaviour between experimental and control practices. We will minimise this potential bias by recruiting patients through searching GP records, rather than by direct GP referral. This method was also the most productive when we tested a range of recruitment methods in our pilot trial [17]. We will identify suitable patients by examining electronic case records for all patients in each general practice. The search will be limited to patients seen by their GPs in the previous four weeks who have been allocated a 'Read Code' for depression, and will be conducted by practice staff or Clinical Studies Officers blind to the random allocation of the GP surgery.

Identified patients will receive a letter from their GP surgery inviting them to take part in the study, enclosing a patient summary sheet outlining the study with a 'Permission for researcher to contact' form to allow a researcher to contact them. Recruitment which requires patients to return paper forms is known to have a very poor response rate, typically only 15% of those contacted will agree to be contacted, a threat to the study's external validity. A recent review of RCT recruitment methods [26] showed that the only likely method of improving recruitment was through telephone reminders by clinicians to non-responders. Consequently, in order to make our sample more representative of a primary care depressed population, we will attempt to enhance our response rate through telephone follow up by practice staff or Clinical Studies Officers.

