### Allocation

Once the baseline assessments are complete, the participant's details will be entered into our automated allocation service via telephone or the internet. Each participant will be assigned an ID number and if their practice is one assigned to collaborative care then the participant's details will be automatically sent to the relevant case manager to alert them to contact this person. All new participants' details are also sent to the trial coordinator and their GP will be informed of their involvement in the study.

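### Blinding the record search does not protect the step before it: GPs who probably know their arm can still influence, by coding and recall, who enters the search pool

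*Protocol article*

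**What the plan says.** All places are in the protocol article.

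- **The threat.** Patient Identification and Recruitment states: "Cluster trials are vulnerable to selection bias through systematic differences in referral behaviour between experimental and control practices".
- **The remedy.** The same section continues: "We will minimise this potential bias by recruiting patients through searching GP records, rather than by direct GP referral". The record search is the only route of entry described.
- **The search terms.** "The search will be limited to patients seen by their GPs in the previous four weeks who have been allocated a 'Read Code' for depression". The four-week limit is attached to the visit. No date limit is given for the code.
- **The blinding.** The search "will be conducted by practice staff or Clinical Studies Officers blind to the random allocation of the GP surgery". Nothing is said about the GP who sees and codes the patient.
- **Practice allocation.** Randomisation of GP Practices: "We will allocate practices by minimisation, with a random element, on centre, deprivation and practice size". No order relative to the searches is given.
- **Patient entry.** Under Allocation, once baseline is complete, "if their practice is one assigned to collaborative care then the participant's details will be automatically sent to the relevant case manager". The GP is also told that the patient has joined.
- **Eligible patients.** Patient inclusion criteria: "We will include both patients newly identified as depressed, with or without one or more previous depressive episodes". Patients with an existing diagnosis that is not responding are eligible too.
- **Primary analysis.** Statistical analysis of clinical data names one covariate, the individual baseline depression score.

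**The concern.** The plan correctly sees that GPs may act differently once their practice has an arm, but it treats this as a matter of referral. Replacing referral by a record search moves the GP's influence back one step, to who is seen and who receives a depression code. A GP with a new service on offer has a reason to code a borderline case or call a patient back. A GP in a control practice does not. A searcher who is blind to arm retrieves that difference faithfully.

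At stake is the comparability of the arms. Newly recognised episodes and long-standing non-responders are both eligible and may have different expected four-month PHQ-9 scores at the same baseline score. If the mix differs by arm because of the allocation, adjustment for baseline PHQ-9 removes the severity difference but not the remaining prognostic one.

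**Working it through.** **1. Is the arm fixed, and probably known to the GP, when patients are identified?** No section says so outright. Four places point that way.

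- Patient Identification and Recruitment speaks of the surgery's random allocation as something the searcher must be blind to.
- Allocation treats the practice's arm as already set when a patient is entered.
- The intervention is described in the abstract as "a combination of case manager coordinated support and brief psychological treatment, enhanced specialist and GP communication", and Intervention - Case Management has the case manager working with GPs on medication problems. An intervention GP can hardly remain unaware of the arm once the first patients are enrolled.
- Forecast execution dates gives 18 months of recruitment. That is 18 × 52/12 = 78 weeks, or 78/4 = 19.5 four-week windows, so repeated searches are plausible.

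The rationale for clustering, under Study Design, adds to this. The investigators concluded that part of the pilot effect came through organisational change in the practice. A design that expects practice behaviour to change cannot simply assume that coding and recall do not.

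**2. Do later steps repair it?** The CIS-R confirms that a patient who was found is depressed, which limits false inclusion. It cannot recover depressed patients who were never coded or seen.

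**3. How many patients must the search supply?** 550 patients / 48 practices = 11.46 per practice. At the 15% agreement to contact quoted for paper forms, 11.46/0.15 = 76 invitations per practice, even if every contact enrols. Telephone follow-up is planned to raise that rate; at an assumed 30% the figure is 11.46/0.30 = 38. No list size or coding rate is given, so neither figure proves that repeated searches are needed.

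**4. What would an imbalance do?** The plan's own numbers come first. An effect of 0.4 SD at 90% power and two-sided alpha 0.05 gives 132 per group, as stated. Then 264 × the stated design effect 1.65 = 435.6, close to the stated 440, and 440/0.80 = 550. (The stated cluster size and ICC give 1 + 13 × 0.06 = 1.78, not 1.65. That is a separate matter and barely changes what follows.)

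With 220 analysed per arm, SE = √(2 × 1.65/220) = 0.1225 SD. For a residual imbalance b after baseline adjustment:

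- type I error = Φ(−1.96 + b/SE) + Φ(−1.96 − b/SE)
- power, if b runs against the intervention = Φ((0.4 − b)/SE − 1.96)

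| b (SD) | Share of 0.4 | Type I error | Power |
|---|---|---|---|
| 0 | 0% | 0.050 | 0.904 |
| 0.05 | 12.5% | 0.069 | 0.815 |
| 0.10 | 25% | 0.129 | 0.688 |
| 0.20 | 50% | 0.372 | 0.372 |

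At a design effect of 1.78, the type I errors for 0.05 and 0.10 are 0.068 and 0.123.

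One way to reach these values is to assume that a fraction f of intervention participants entered only because of changed coding or recall, and that their outcome differs by 0.5 SD at equal baseline score. Then b = 0.5f: 0.05 at f = 10%, 0.10 at f = 20%, 0.20 at f = 40%. Both f and 0.5 SD are assumptions, and the sign could go either way.

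**The case against.** The strongest reply is that the inference about timing is not secure. The plan expects even practice staff who run a search to be blind to their own surgery's arm. That fits a practice that has not yet been told. The 18 months could also reflect practices joining in turn. This stands as a reason not to state post-allocation, rolling searches as fact. It does not close the gap, because the plan does not require non-disclosure to the GP. Once a practice has its first intervention participant, the GP is told of the enrolment and the case manager becomes active. On this reading, only the earliest search is protected.

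A reader might go further and infer that GPs decide who is found. The document does not support that. The code has no date limit and existing diagnoses qualify, so many codes may predate allocation. GPs make no selection within the search results, a researcher confirms eligibility, and no section describes recall for the trial. The supportable word is influence. A reader might also take the plan to claim that searching removes the bias, but it claims only to minimise it.

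It is also fair to say that Process Data plans to measure duration of depression, and that the analysis section promises practice-level analyses and cluster CONSORT reporting. An imbalance in chronicity could therefore be seen. Seeing it is not preventing it, and no comparison of duration by arm is tied to this bias.

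Finally, export fields and an extra sensitivity analysis may sit in a full protocol or SAP that is not shown. That is true of those details. The point here is that the article states its safeguard and the safeguard does not reach the step where the bias can arise.

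**Conclusion.** The concern holds in a limited form. The stated safeguard covers the searcher, while both search terms are produced by GPs who probably know their arm. Coding and recall therefore remain a route to differential entry. Neither the CIS-R nor adjustment for baseline depression score closes it.

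The conclusion rests on three inferences: that at least some searches follow allocation, that they are repeated, and that intervention GPs know their arm. All are well supported but none is stated. The size and direction of any bias are unknown. The tabulated values show sensitivity to an assumed imbalance and are not estimates of one. This should be changed because the safeguard is cheap. It is not evidence that the trial's result would be biased.

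**What to change.** 1. In Patient Identification and Recruitment, require that each practice's first search be run, and its invitation list frozen, before the practice is told its allocation. Allow later four-week searches only as top-up. This protects the first list fully and the top-up not at all, which is why items 2 and 3 are needed.
2. At every search, record the dates of the qualifying code and of the qualifying visit relative to disclosure of allocation, together with the number of search-positive patients per 1,000 registered. Report these by arm in the cluster CONSORT flow.
3. Add, here or in the SAP, a sensitivity analysis of four-month PHQ-9 restricted to participants whose qualifying code and visit both predate disclosure, or who were on the first list. Restricting on code date alone would leave the visit route open. Compare the already planned duration of depression by arm.
4. Add a sentence acknowledging that record searching reduces differential referral but leaves coding and recall as possible sources of difference.

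The cost is a short delay in telling practices their arm, date fields and a count from searches that are run anyway, and one analysis with lower precision than the primary. No extra patients are needed.
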